###### Clinician Ratings

We will recruit ICU and PCU clinicians as volunteers to review and rate the general quality of a subsample of ICU transfer summaries randomly sampled from the larger pool of sampled summaries. Clinicians will use a 7-point scale to assess five criteria adapted from a previous study evaluating a similar tool [39,55]: organization (ie, presentation was logical and clear), completeness (ie, no information gaps or omissions), pertinence (ie, all content was relevant to patient care), overall satisfaction with the quality of the summary, and degree of confidence that the accepting clinician will understand the patient care plan after reading the transfer summary (see Table 1). Clinicians will be blinded to both the study period and hospital.

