**Methods:**

This study is a cluster-specific pre-post trial, with randomized and staggered implementation of the e-transfer tool in four hospitals in Calgary, Alberta. Hospitals (ie, clusters) were allocated randomly to cross over every 2 months from control (ie, dictation only) to intervention (ie, e-transfer tool). Implementation at each site was facilitated with user education, point-of-care support, and audit and feedback. We will compare transfer summaries randomly sampled over 6 months postimplementation to summaries randomly sampled over 6 months preimplementation. The primary outcome will be a binary composite measure of the timeliness and completeness of transfer summaries. Secondary measures will include overall completeness, timeliness, and provider ratings of transfer summaries; hospital and ICU lengths of stay; and post-ICU patient outcomes, including ICU readmission, adverse events, cardiac arrest, rapid response team activation, and mortality. We will use descriptive statistics (ie, medians and means) to describe demographic characteristics. The primary outcome will be compared within each hospital pre- and postimplementation using separate logistic regression models for each hospital, with adjustment for patient characteristics.

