### Local Initiative to Standardize Transfer Summaries: The Electronic ICU Transfer Tool

In 2017, we began designing an evidence-informed, computer-enabled, ICU-specific communication tool in the primary, integrated patient care CIS—Sunrise Clinical Manager (Eclipsys Corporation)—used in four acute care hospitals in a single Canadian city. This work was initiated as a quality improvement project to improve upon the conventional system of dictation that physicians and NPs—herein called ICU clinicians—use to prepare medical transfer summaries for ICU patients [41]. To dictate a summary, ICU clinicians use eScription, 2010 release (Nuance Communications), a health information management dictation, speech recognition, and transcription (DST) platform. The clinician verbalizes relevant patient transfer information to create a voice file that is run through speech recognition software to create a text report. The report is then edited by a transcriptionist and sent to the designated ICU clinician for approval before being uploaded for electronic viewing in the CIS as well as to a provincial, web-based health data repository accessible by community-based physicians (Alberta Netcare).

The content and structure of the ICU electronic transfer (e-transfer) tool was based on a national survey of existing transfer summary tools [42], subsequent consensus-based recommendations of two independent multidisciplinary groups of health care providers [41,43], and a heuristic evaluation [41]. The e-transfer tool consists of 10 overarching document sections: visit data, goals of care, allergy and intolerances, diagnoses and visit issues, course in ICU, investigations, medications, discharge to home or community, send copies to, and completion. These sections are designed with a user interface combination of structured fields (eg, checkboxes); automated fields, which pull in relevant patient data from other CIS locations; and free-text fields (see Figure 1). The tool permits ICU clinicians to open an ICU summary as a clinical document directly in the patient’s EMR and edit the summary over the course of the patient’s ICU stay. As with the DST system, the designated ICU clinician must approve transfer summaries. The summaries remain in the CIS and are uploaded to the provincial repository.

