### E-Transfer Tool Implementation

The e-transfer tool has been sequentially implemented into the four study hospitals at a new site every 2 months. This occurred between July 2018 and January 2019. The study biostatistician (AS), who was not involved with clinical practice in the ICUs, randomized the order of hospitals for implementation. Dictation remained available after implementation, but the ICU e-transfer tool was endorsed as the primary method to prepare ICU transfer summaries; as well, use of the tool was supported with strategies that have been successfully used in previous local initiatives, including in-person and web-based education, point-of-care support, and electronic audit and feedback [50].

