### Data Collection

#### Overview

We set pre- and postimplementation data collection periods to extend for 6 months each, based on the staggered dates when the ICU e-transfer tool was implemented at each hospital. Patients transferred from the ICU prior to the intervention implementation date of their hospital are considered in the preimplementation period, while patients transferred from the ICU on or after the intervention implementation date of their hospital are considered in the postimplementation period.

Data collection involves (1) electronic extraction from provincial system repositories and a local critical care database, (2) manual abstraction from the patient’s electronic and paper medical record by trained researchers, and (3) manual rating of sampled transfer summaries by clinicians. Survey data of ICU clinician perspectives was collected pre- and postimplementation of the e-transfer tool. The flow of data collection is shown in Figure 2. Where feasible, we are deidentifying hospital name, dates, and clinician and patient identifiers from clinical documents (eg, transfer summaries and clinician progress notes) secured for manual data abstraction. All data will be encrypted and retained in a secured office.

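### Clinician raters are said to be blinded to study period, but the document format they must see reveals the period of every e-transfer summary, so that blinding is at best partial

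*Protocol article*

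**What the plan says.** Under Clinician Ratings, volunteer ICU and PCU clinicians score a random subsample of summaries on five criteria, each on a 7-point scale. The blinding statement is unqualified: "Clinicians will be blinded to both the study period and hospital". One of the five criteria is "organization (ie, presentation was logical and clear").

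Other parts of the article bear on that statement:

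- **Abstract, Methods.** Hospitals cross over "from control (ie, dictation only) to intervention (ie, e-transfer tool").
- **Introduction, Local Initiative.** Dictating clinicians "create a voice file that is run through speech recognition software to create a text report", which a transcriptionist then edits. By contrast, "The e-transfer tool consists of 10 overarching document sections", built from structured, automated and free-text fields.
- **Data Collection, Overview.** The only masking step described is that, where feasible, "we are deidentifying hospital name, dates, and clinician and patient identifiers from clinical documents".
- **E-Transfer Tool Implementation.** After go-live "the ICU e-transfer tool was endorsed as the primary method to prepare ICU transfer summaries", although dictation could still be used.
- **Completeness of Information.** The researchers who abstract completeness are openly said not to be blinded to period or hospital. No such qualification is made for the raters.
- **Sample Size Calculations.** 64 summaries per period are to be rated.

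**The concern.** Taking dates and hospital names off a page does not hide what kind of page it is. The two preparation methods give visibly different documents, and by the article's own definition one of them belongs to the control period. A rater who recognises the tool's layout knows that the summary comes from after implementation.

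The five criteria are opinions. If raters expect the new tool to be better, that expectation would raise postimplementation scores and could not be told apart from a real gain in quality. A reader who relies on the blinding statement would discount this possibility when the design does not allow it to be discounted.

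**Working it through.** **1. Does the described masking cover the feature that identifies period?**

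| Question | What the article describes |
|---|---|
| Format before go-live | Dictation only: a transcribed text report |
| Format after go-live | Tool as primary method: 10 sections, checkboxes, automated fields; dictation still possible |
| What is removed | Hospital name, dates, clinician and patient identifiers, where feasible |
| What raters must judge | Among other things, whether the presentation is logical and clear |

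Format is not among the things removed. The organization criterion means that raters have to see the layout. It follows that:

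- Tool format implies postimplementation.
- Dictated format implies pre *or* post, because dictation remained available.
- Hospital cannot be read from format, since all four hospitals use the same tool and the same dictation system.

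The unmasking is therefore one-sided, and its extent depends on tool uptake, which the article does not give.

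**2. How often would format give away the period?** Let *u* be the share of rated postimplementation summaries made with the tool (assumed). With 64 summaries per period, call every tool-format summary post and every dictated one pre. All 64 pre summaries and 64*u* post summaries are then classified correctly:

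(64 + 64*u*) / 128 = (1 + *u*) / 2

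This gives 75% at *u* = 0.5, 90% at *u* = 0.8 and 100% at *u* = 1, against 50% by chance. It assumes that raters know which format goes with which period.

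**3. The plan's own sample size.** Inputs from Sample Size Calculations: difference 0.5, SD 1, power 80%, α 5% (two-sided assumed, as sidedness is not stated).

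n per period = 2(1.960 + 0.842)² × 1² / 0.5² = 62.8, so 63 by the normal approximation. The two-sample t-test version gives 63.8, so 64. At 64 v 64 the t-test power is 80.1%. The stated 64 + 64 is reproduced.

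**4. Illustration of what expectation could do.** Assume no true difference. Each tool-format summary is rated *b* points higher because the rater recognises it, and dictated summaries are not shifted. Then:

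- mean difference d = *u* × *b*
- standard error = √(2/64) = 0.177
- chance of a significant result = Φ(d/0.177 − 1.96) + Φ(−d/0.177 − 1.96)

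| *u* (assumed) | *b* (assumed) | d | d / 0.177 | Chance of p < 0.05 |
|---|---|---|---|---|
| 0.5 | 0.10 | 0.050 | 0.28 | 6% |
| 0.8 | 0.10 | 0.080 | 0.45 | 7% |
| 1.0 | 0.10 | 0.100 | 0.57 | 9% |
| 0.5 | 0.25 | 0.125 | 0.71 | 11% |
| 0.8 | 0.25 | 0.200 | 1.13 | 20% |
| 1.0 | 0.25 | 0.250 | 1.41 | 29% |

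The noncentral t gives the same rounded values for the 0.25-point rows (10.8%, 20.2%, 28.9%). The nominal rate is 5%.

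**The case against.** **The article does not say how summaries are shown to raters.** The de-identification sentence concerns documents secured for manual abstraction, and clinician rating is listed as a separate activity. An article may leave presentation details to the full protocol, so summaries might be reformatted first. This stands in part: the masking procedure for raters is inferred. But the blinding claim is made here, without qualification, and full reformatting would sit badly with a criterion that asks about presentation. If it is done, the article needs to say so and explain how organization is then scored.

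**The claim is about period, not method.** True, and it limits the point. A reader might infer that raters can identify the period of every summary. The documents do not support that, because a dictated summary can come from either period.

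**The tool was piloted earlier in one ICU.** A reader might infer that the layout cannot exist before go-live. The Introduction reports a pilot without dates, so that is too absolute. The Abstract's definition of control as dictation only still makes tool format a marker of the post period in this study.

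**Raters may not know the tool.** The article does not say where they are recruited. Local clinicians would probably recognise it, but that is an assumption.

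**The percentages do not describe the planned analysis.** Correct. The shifts and uptake have no source in the article, and the test is unadjusted. Data Analysis plans within-hospital and pooled models with adjustment for patient characteristics. Adjustment of that kind would not remove a bias tied to format, but the figures remain illustrative.

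**The outcome is secondary.** Correct. It would also be wrong to call it the trial's most subjective outcome, since the survey in which ICU clinicians rate their own last summary is at least as subjective and claims no blinding.

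**Conclusion.** The concern holds in a limited form. The article states that raters are blinded to study period, and the design it describes delivers this only in part: tool-format summaries disclose their period and dictated ones do so only probabilistically. This rests on the article's own account of the two formats, its definition of control, the masking it lists and the organization criterion. It assumes that raters see the summaries in recognisable form.

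The size of any resulting bias cannot be derived from the documents. Under the assumed 0.25-point shift, the false-positive rate would be about 11% to 29% as uptake goes from 50% to 100%. With a 0.10-point shift it would be about 6% to 9%. These are not estimates for this trial.

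A reader might go further and infer that blinding to hospital fails or that the primary composite is compromised. Neither follows. Format does not identify hospital, and the primary composite does not use these ratings. The point concerns what may be claimed for one set of secondary ratings on 128 summaries.

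**What to change.** 1. **Restate the blinding.** Say that raters are masked to hospital, dates and identifiers but not to document format, so that blinding to study period is at best partial. If summaries are reformatted before rating, describe how and say how organization is still judged. Cost: a sentence or two.
2. **Add one item to the rating form** recording the rater's guess of period or preparation method. Cost: one line for each of 128 summaries. Guesses may partly reflect real quality differences, so they describe the extent of unmasking and do not correct for it.
3. **Report the ratings as not fully blinded**, with expectation bias named as a limitation and tool uptake in the rated subsample shown beside the result. The article already plans to record the preparation method for every transfer, so this needs no new data.

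Presenting summaries as plain text for the criteria that do not depend on layout is optional. The tool's section headings may survive the conversion, structure is part of what the tool offers, and it adds work for volunteers. If it is used, all plain-text ratings should be finished before any original layout is shown, otherwise the second view unmasks later ratings.

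The article describes the rating step in the future tense and says outcome abstraction is underway, so items 1 and 3 are open and item 2 is possible if rating has not begun.

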##### Patient Outcomes

Incidents of ICU readmissions and rapid response team activations occurring within 3 days of ICU transfer were extracted from the critical care system repository; cardiac events within 3 days of ICU transfer were extracted from the *Code Blue* database maintained within the Department of Critical Care Medicine (see Table 1). Patients who were readmitted to the ICU within 3 days of their first ICU transfer will be further evaluated by a clinician (see Figure 2) to determine if the reason for their readmission was related to a health issue documented in the transfer summary of their first ICU admission; this will be recorded as *yes*, *no*, or *unclear*.

Adverse events within 3 days of ICU transfer will be abstracted using a two-stage manual abstraction process based on the Institute for Healthcare Improvement Global Trigger Tool (GTT) method of chart review [56]. The GTT definition of an adverse event, as described on page 5 of the Institute for Healthcare Improvement white paper [56], is “any unintended physical injury resulting from or contributed to by medical care that requires additional monitoring, treatment or hospitalization, or that results in death.” In Stage 1, two trained researchers will independently review the daily clinician progress notes charted in each patient’s paper medical record 3 days post–ICU transfer. Using a list of 19 patient safety indicators, they will identify and record *yes*, *no*, or *unsure* for each incident of a suspected adverse event. The patient safety indicators are based on Southern and colleagues’ [57] list of 18 triggers adapted to a Canadian context with newer iterations of health coding data, with the addition of “patient falls.” In order to ensure good interrater reliability, Stage 1 reviewers will appraise a small sample of charts, compare results, and resolve any discrepancies before moving forward to evaluate the full sample. In Stage 2, any suspected adverse event recorded as *yes* or *unsure* during Stage 1 will be flagged for review by a third reviewer who will be a clinician. The clinician will review the notes and evaluate each suspected adverse event to confirm or reject the occurrence of the event using the GTT definition. In cases with a confirmed adverse event, the clinician reviewer will determine if the adverse event was preventable (ie, *yes*, *no*, or *unsure*), as well as designate the severity of the adverse event using the GTT categories of harm [56].

ICU and hospital length of stay will be captured using ICU and hospital admission and discharge dates and times. In-hospital mortality will be captured as the time from ICU discharge to hospital mortality, with censoring at hospital discharge for those who survived hospital.

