#### Patient Demographics

Patient demographic data includes the following: age; sex; ICU and hospital admission and discharge dates, times, and locations; hospital mortality; comorbidities; ICU interventions (ie, intubation, ventilation, vasoactive medications, and dialysis); and severity of illness measures, including the Acute Physiology and Chronic Health Evaluation II (APACHE II) score [51], the Glasgow Coma Scale (GCS) score [52], and the Sequential Organ Failure Assessment (SOFA) score [53].

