**Patient outcomes**		
	Occurrence of negative patient outcomes within 3 days post–ICU transfer (%)	Patient events occurring within 3 days post-ICU: ICU readmission Adverse events Rapid response team activation Cardiac arrest
	Hospital and ICU total length of stay (in days)	Time between admission and discharge
	Mortality (in hours)	Time from ICU transfer to hospital mortality
ICU clinicians’ perceptions of their last transfer summary		Rate seven criteria on a 7-point Likert scale: Process: understood process to produce high-quality summary Workload: manageable to complete within routine ICU workflow Effectiveness: format able to communicate all relevant information clearly and logically Revisions: able to revise as new information becomes available Timely: able to complete at the time of patient transfer from ICU Satisfaction: produced a high-quality summary Confident that receiving PCU team will understand the patient care plan Length of time required to complete last transfer summary, including gathering all relevant information

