#### Sample Size Calculations

Sample size calculations were based on the cluster-specific pre-post study design. Based on our pilot [41,42], we calculated a required sample size of 144 pre- and 144 postimplementation ICU transfer summaries from each hospital to assess our primary outcome. This will be sufficient to detect an absolute difference in our primary outcome of 15% for each hospital with 82% power and an α value of 5% based on a baseline proportion of 20%; we observed a change in our pilot from 23% to 83%. A random sample of 24 ICU patients per hospital per month, over 6 months pre- and 6 months postimplementation, will facilitate secondary analyses, which accommodate the possibility of secular trends. The study biostatistician (AS) determined the random sample by assigning computer-generated random numbers to the complete list of patients transferred from each ICU within the study period, which was extracted by a data analyst with the critical care analytics system (see Figure 2). The study biostatistician was blinded to the method used to create the summary at the time of randomization.

To collect clinician ratings of the transfer summary quality, we calculated requiring 64 summaries preimplementation (ie, 16 per hospital × 4 hospitals = 64) and 64 summaries postimplementation (ie, 16 per hospital × 4 hospitals = 64), which will be sampled from aforementioned summaries, to detect an absolute difference in means as small as 0.5, assuming an SD of 1, with 80% power and an α value of 5%. The same patient cases will be used to assess for suspected post-ICU adverse events.

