#### Data Analysis

Demographic characteristics pre- and postimplementation for each hospital will be described using medians with IQRs, means with SDs, and frequencies with percentages, as appropriate. The primary outcome will be compared within each hospital pre- and postimplementation using separate logistic regression models for each hospital, with adjustment for the following patient characteristics: age, sex, reason for ICU admission, status on ICU admission (ie, Charlson Comorbidity Index, APACHE II, GCS, and SOFA), therapies received while in ICU (ie, ventilation, vasoactive medications, intermittent hemodialysis, and continuous renal replacement therapy), status on transfer (ie, transfer delay time, transfer decision cancellations, and ICU occupancy), and ICU length of stay. Pooled analyses across all four hospitals will use mixed-effects logistic regression models with a fixed effect for intervention and a fixed effect for time in months, in order to model the underlying secular trend. A fixed effect for patient characteristics will also be used, as noted above, and random effects will be used for hospital and hospital by time to account for intracluster and interperiod correlation. In case of poor model fit or convergence issues due to a limited number of clusters, hospital-level analyses will be considered by aggregating the primary outcome over all summaries in each hospital during each month and using linear regression of the aggregated cluster-period proportions of complete and timely summaries with fixed effects for hospital and time in months. Secondary outcomes will be analyzed as described for the primary outcome, using within-hospital and pooled analyses. Wilcoxon rank-sum tests will be used to compare ICU and hospital length of stay, and log-rank tests will be used to compare time from ICU discharge to hospital mortality.

Open-ended comments collected through clinician surveys will be analyzed according to standard practices of qualitative textual analysis.

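### The log-rank test with survivors censored at discharge compares daily death rates among patients still in hospital, not the risk of dying in hospital, and it can mislead if discharge timing shifts between periods

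*Protocol article*

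**What the plan says.** Table 1 lists mortality as a patient outcome, in hours: "Time from ICU transfer to hospital mortality". The Patient Outcomes text adds the censoring rule: "time from ICU discharge to hospital mortality, with censoring at hospital discharge for those who survived hospital". Data Analysis names the test: "log-rank tests will be used to compare time from ICU discharge to hospital mortality".

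Three other statements bear on this:

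- Hospital stay is itself compared between the same two periods: "Wilcoxon rank-sum tests will be used to compare ICU and hospital length of stay".
- A general rule sends secondary outcomes to the logistic models: "Secondary outcomes will be analyzed as described for the primary outcome, using within-hospital and pooled analyses". The next sentence then gives length of stay and mortality their own tests.
- Hospital mortality is among the patient data collected ("hospital mortality; comorbidities; ICU interventions", Patient Demographics).

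Nothing in the article treats live discharge as a competing event.

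**The concern.** Ordinary censoring means that the event could still happen but was not observed. Here the event is death in hospital, and a patient who has gone home alive cannot have it. These patients left because they recovered, so they differ from those who remain.

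The log-rank test then compares death rates per day among patients still in a bed. That is a legitimate quantity (the cause-specific hazard), but it is not what a reader of a mortality result wants to know, which is whether fewer patients die.

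The two answers separate when discharge timing differs between periods. This trial is open to that. It is a before-and-after comparison, the article allows for secular trends, and length of stay is one of its outcomes. The log-rank test as described has no term for calendar time. At stake is a false harm signal, or a missed benefit, on the gravest patient outcome in the plan.

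**Working it through.** **1. The plan's own figure.** The only power statement for the tool's effect on summaries concerns the primary outcome: "144 pre- and 144 postimplementation ICU transfer summaries from each hospital", to "detect an absolute difference in our primary outcome of 15% for each hospital", from a 20% baseline with 82% power. For 20% versus 35%, the mean proportion is 0.275 and two-sided 5% is assumed:

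- z = [0.15 × √144 − 1.96 × √(2 × 0.275 × 0.725)] / √(0.20 × 0.80 + 0.35 × 0.65)
- z = (1.800 − 1.238) / 0.622 = 0.90, so power is 81.7%.

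The stated figure is reproduced. No mortality rate, event count or mortality power is given.

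**2. Numbers available for mortality.** Four hospitals × 144 = 576 patients per period. At an assumed 6% to 10% in-hospital mortality that is 576 × 0.06 = 35 to 576 × 0.10 = 58 deaths per period. In one hospital it is 144 × 0.06 = 9 to 144 × 0.10 = 14.

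**3. Mechanism.** At each death time the log-rank test expects the later period to supply the share n_post / (n_pre + n_post) of the deaths, where n counts patients still in hospital. Suppose the same patients die on the same days in both periods but survivors leave earlier in the later one. Then n_post is smaller, the expected share falls below one half, and the observed half counts as an excess.

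**4. Size with fates fixed.** This is a simulation with clustering ignored. Assumptions not in the documents: mortality 6% to 10%, survivors' ward stay median 8 days, time to death median 7 or 12 days, log-SD 0.9. Deaths and death times have the same distribution in both periods, and only survivors' stay is shortened.

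| Survivors' stay in later period | Patients per period | Log-rank finds later period significantly worse (nominal 2.5%) |
|---|---|---|
| 10% shorter | 576 | about 7% |
| 20% shorter | 576 | about 15% to 26% |
| 20% shorter | 144 (one hospital) | about 8% |

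Repeat runs of the 20% case at 576 per period spanned 12% to 28% at the widest. A two-proportion comparison stays near 5% total rejections throughout.

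A different time model (exponential, mean 14 days to exit, mortality 5% to 12%) gives 14% to 23% when survivors leave 1.25 times as fast. Since 1 / 1.25 = 0.80, this is the same 20% shortening.

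**5. A real benefit.** Let mortality fall from 10% to 7% with a 20% shorter stay, under the settings of step 4. The log-rank test rejects in about 6% of trials (median death time 12 days) to 11% (7 days), against about 44% for the proportions. Its mean Z is about −0.37 to −0.75, so it still points towards benefit.

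**6. When the sign changes.** In the exponential model, take 8% mortality and a true relative reduction of 15%. Mean Z is −0.73 with unchanged discharge, +0.27 at 1.25 times as fast and +1.18 at 1.5 times. At 1.5 times the later period is called significantly worse in 22% of runs.

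**7. When there is no distortion.** Keep the daily death hazard at 0.08 / 14 and raise only the discharge rate by 1.25. The proportion dying becomes 0.08 / (0.08 + 0.92 × 1.25) = 0.08 / 1.23 = 6.5%. The log-rank test stays at about 4% to 5% total rejections. The comparison of proportions declares a benefit in about 15% of runs, because fewer patients do die in hospital.

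**The case against.** The strongest defence is that a log-rank test with live discharge censored is a valid test of the cause-specific death hazard. That is correct. A reader might infer that the test is invalid as such, or that any change in discharge practice biases it. Step 7 shows otherwise: with an unchanged daily death hazard it keeps its level. Longer stays would push the distortion the other way. The objection that survives is narrower: the quantity tested is not the risk of dying in hospital, and the plan does not say so.

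A reader might also infer that the test reverses the answer. Step 5 shows lost power rather than reversal. A sign change needs a small true benefit together with a sizeable discharge shift, as in step 6.

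Nor does the article say that the tool will shorten stay. It lists and compares length of stay, and the 10% and 20% shifts are assumptions.

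A benefit or harm would not be wholly hidden. Hospital mortality is among the patient data, which the plan describes by period and hospital with frequencies and percentages, and length of stay is compared separately. A careful reader could see a discordance. The formal mortality test would still be the log-rank.

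Finally, the general rule for secondary outcomes might be read as sending mortality to the logistic models as well. The specific sentence on the log-rank test follows it and names mortality, so the general rule does not settle the matter. A fuller analysis plan may add detail, but the censoring rule and the test are stated here, not left open.

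**Conclusion.** The point holds as a should-fix on a secondary outcome. The planned test answers a question about daily death rates among patients still in hospital, and the article presents it as the comparison of in-hospital mortality.

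The practical damage depends on discharge timing and on mechanism. With fates fixed and survivors' stay 20% shorter, the false-worse rate is about 15% to 26% pooled and about 8% in a single hospital. With a 10% shift it is about 7% pooled. With no shift there is none. These figures rest on assumed mortality, ward stay and death times, and they ignore clustering. The primary outcome is unaffected, and no sample-size claim is attached to mortality.

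**What to change.** In Patient Outcomes and Data Analysis, replace the censored log-rank test as the mortality comparison by one of these:

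- in-hospital death after ICU transfer as a yes/no outcome, analysed with the within-hospital and pooled logistic models already in the plan; or
- the cumulative incidence of in-hospital death with live discharge as a competing event, compared by Gray's test stratified by hospital.

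The log-rank test may stay as a cause-specific hazard analysis if it is labelled as such and reported beside the comparison of time to discharge.

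The cost is about two sentences. Death status and discharge dates and times are already collected.

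There are three downsides:

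- The yes/no version loses timing.
- In-hospital death as a proportion can itself fall because patients leave sooner (step 7), so it must be read with length of stay. Mortality at a fixed time would avoid this but needs vital status after discharge, which the article does not say is available.
- At the assumed rates, one hospital has about 2 × 9 = 18 to 2 × 14 = 28 deaths over both periods. That is few for the full list of adjustment variables, so the within-hospital mortality models would need a shorter list.
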